## Statistical principles

### Overall principles

After completion of the trial, all the statistical analysis tests will use two-sided tests with a nominal alpha level of 0.05, using the SAS [10, 12]. All confidence interval (CI) reports will be 95% CIs. For each outcome, the null hypothesis is the absence of difference between the intervention groups.

The description of measurement indicators will calculate the mean, standard deviation, median, minimum, maximum, and interquartile range (Q3–Q1). Normal continuous variables will be presented as the mean and standard deviation; non-normally distributed continuous variables will be presented as median with interquartile range. Counting indicators will be presented as the frequency and percentage of each category.

Inter-group comparisons will be performed with independent two-sample *t*-tests (normality, homogeneity of variance) or Wilcoxon rank-sum test (non-normality, heterogeneity of variance). Comparisons within normal and nonnormally distributed groups will be performed using paired *t*-test and paired rank-sum test, respectively. *χ*^2^ test or Fisher’s exact probability will be needed for count metrics, and the Wilcoxon rank-sum test will be used for categorical variables. A generalized linear mixed model analysis will be performed on the repeated measured outcome.

In situations where an imbalance in the baseline indicators exists, an adjustment will be required for the efficacy comparison of variables, such as age, sex, and concomitant treatment. The covariance method will be used for continuous variables, and logistic regression analysis was used for count metrics and hierarchical metrics.

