### Baseline characteristics

The baseline characteristics of all participants in both groups will be shown in Table 2. The table will describe the following variables: age, height, weight, BMI, female sex, nationality, heart rate, systolic blood pressure, diastolic blood pressure, mean arterial pressure, respiration rate, drug or constitution allergic history, comorbid conditions, and concomitant treatment. The sample will be described according to the full analysis set. The baseline characteristics will be compared between groups.

**Table 2 Tab2:** Baseline characteristics of participants prior to treatment

Characteristic	SZF, number, central tendency (variability)	Irbesartan, number, central tendency (variability)	All participants, number, central tendency (variability)	***p*** value
	*n* = xx	*n* = xx	*n* = xx	

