## Analysis methods

### Outcome measure analyses

#### Primary outcome analyses

The primary analysis will be conducted in the FAS and PPS. The change in 24-h UP (mg/24 h) is the primary outcome. The distribution and changes of 24-h UP at weeks 0, 4, 8, 12, 16, 20, and 24 of medication will be described. Intra- and inter-group comparisons will be made. The distributions of qualitative judgments of 24-h UP at weeks 4, 8, 12, 16, 20, and 24 will be described and compared between groups. The baseline 24-h UP is essential to assess the progression of UP; therefore, analysis of covariance (ANCOVA) will be performed to analyze the 24-h UP change from baseline to week 24, using baseline 24-h UP as a covariate. Interactions between site and group will also be tested.

Table 3 provides a reference for the qualitative determination of the variation. The efficiency rate will be calculated by summing the rate of clinical control, obvious therapeutic effect, and therapeutic effect (Table 4).

**Table 3 Tab3:** 24-h UP qualitative judgments classification standard

Qualitative judgment	Standard
Clinical control	24-h UP< 0.5 g
Obvious therapeutic effect	24-h UP reduction ≥ 50%
With therapeutic effect	24-h UP reduction ≥ 20%
Invalid	Fail to reach the standards above

**Table 4 Tab4:** Analysis of primary outcome

Time point	SZF, number, mean (SD)	Irbesartan, number, mean (SD)	Mean difference (95% CI)	***p*** value
Visit at	*n* = xx	*n* = xx		
Week 0	xx (xx)	xx (xx)	xx (xx to xx)	.xx
Week 4 ^a^	xx (xx)	xx (xx)	xx (xx to xx)	.xx
Week 8	xx (xx)	xx (xx)	xx (xx to xx)	.xx
Week 12	xx (xx)	xx (xx)	xx (xx to xx)	.xx
Week 16	xx (xx)	xx (xx)	xx (xx to xx)	.xx
Week 20	xx (xx)	xx (xx)	xx (xx to xx)	.xx
Week 24	xx (xx)	xx (xx)	xx (xx to xx)	.xx
Overall SZF effect^b^				.xx

^a,b^*p* values comparing between group differences at visit points post-randomization (a) and over the entire24-week trial (b: primary outcome)

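### Beyond baseline 24-h UP, covariate adjustment of the efficacy comparison is triggered by an undefined baseline imbalance and drawn from an open list, so the adjusted model depends on chance differences

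*Protocol article*

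**What the plan says.** All references are to the Protocol article, which presents the trial's analysis plan.

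- **Overall principles** sets the rule: "In situations where an imbalance in the baseline indicators exists, an adjustment will be required for the efficacy comparison of variables", continuing "such as age, sex, and concomitant treatment". No criterion for imbalance is given, and the wording leaves the list open. The method follows: "The covariance method will be used for continuous variables, and logistic regression analysis was used for count metrics and hierarchical metrics".
- **Baseline characteristics** adds: "The baseline characteristics will be compared between groups". The Table 2 shell has a p-value column, and its title is "Baseline characteristics of participants prior to treatment". Concomitant treatment is one of its blocks.
- **Overall principles** also sets the significance level: "all the statistical analysis tests will use two-sided tests with a nominal alpha level of 0.05".
- **Primary outcome analyses** specifies an ANCOVA of the week-24 change, "using baseline 24-h UP as a covariate", with no condition attached. It adds: "Interactions between site and group will also be tested".

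**The concern.** In a randomised trial, a difference between arms in age, sex or any other pre-treatment variable arises by chance. Its size or p-value says nothing about how strongly the variable predicts 24-h UP, which is the only reason to adjust for it. A rule that adjusts when imbalance is seen can bring in variables with no prognostic value and leave out prognostic ones that happen to be balanced.

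Two things are at stake. The first is prespecification. The Abstract and Background say the plan exists to prevent selective reporting and analysis steered by the data, yet this rule lets the data choose part of the model. If the trigger fires, the reader also has two candidate results, the ANCOVA with baseline 24-h UP alone and the further-adjusted comparison, and nothing says which one governs. The second is precision: the gain from adjusting for prognostic covariates is available in every trial, but the rule collects it only when chance has produced an imbalance.

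**Working it through.** **Inputs.** From the article: 120 patients allocated 1:1 (60 per arm); a two-sided 0.05 level; three variables named as examples in the rule; and 13 named Table 2 rows (age, height, weight, BMI, sex, nationality, heart rate, systolic, diastolic and mean arterial pressure, respiration rate, allergic history, diabetic retinopathy) plus open rows. The sample size calculation is left to the earlier published protocol, so 120 cannot be reproduced here; the point does not rest on it.

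**Step 1: how often chance would fire the trigger.** Assume that imbalance means p < 0.05 on a baseline test. For k independent tests under valid randomisation, the probability of at least one is 1 − 0.95^k.

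- k = 3: 1 − 0.95^3 = 0.143
- k = 8: 1 − 0.95^8 = 0.337
- k = 10: 1 − 0.95^10 = 0.401
- k = 13: 1 − 0.95^13 = 0.487

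The 13 rows are not independent: BMI is computed from height and weight, and mean arterial pressure normally from systolic and diastolic pressure. If they behave like 8 to 10 independent tests (an assumption), the figure is 34% to 40%.

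**Step 2: what the rule does to error and power.** A simulation used 60 patients per arm and 8,000 runs per scenario. Assumptions: outcome SD 1; correlation 0.5 between baseline 24-h UP and outcome; three further independent covariates, each with correlation r with the outcome; and a true effect of 0 or 0.45 SD. Three ANCOVAs were compared: baseline 24-h UP only; plus all three covariates always; and plus only those with baseline p < 0.05.

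| r | Type I error: baseline only / always / triggered | Power: baseline only / always / triggered |
|---|---|---|
| 0.1 | 4.9% / 4.8% / 4.9% | 80.6% / 80.7% / 80.3% |
| 0.2 | 4.7% / 4.7% / 4.4% | 80.4% / 85.9% / 81.0% |
| 0.3 | 5.3% / 5.5% / 4.3% | 81.0% / 93.4% / 82.5% |
| 0.4 | 5.4% / 5.4% / 3.5% | 80.6% / 99.6% / 83.3% |

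The Monte Carlo standard error is √(0.05 × 0.95 / 8000) = 0.24 percentage points near 5%, and √(0.8 × 0.2 / 8000) = 0.45 points near 80%.

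**Step 3: hand check at r = 0.3.** Residual variance is 1 − 0.5² = 0.75 with baseline only, and 0.75 − 3 × 0.3² = 0.48 with all three covariates. The standard errors of the group difference are √(0.75 × 2/60) = 0.158 and √(0.48 × 2/60) = 0.126. The ratios 0.45/0.158 = 2.85 and 0.45/0.126 = 3.56, against a critical value of about 1.98, give power of about 81% and 94%. These agree with the simulated 81.0% and 93.4%.

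The triggered rule stays close to the baseline-only model because its condition is met in only about one run in seven (13% to 15% in the simulation).

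**The case against.** The strongest defence is that the main covariate is already fixed. Baseline 24-h UP enters the primary ANCOVA whatever the baseline table shows. This stands, and it limits the point to further adjustment. A reader who saw only the Overall principles section might infer that the primary model has no prespecified covariate; the Primary outcome analyses section rules that out.

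Four further inferences are tempting, and the documents do not support them.

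- **That p < 0.05 is the trigger.** The article gives no criterion. The p-value column makes this reading likely, but it remains an assumption, and the full analysis plan, which is not shown, may define imbalance.
- **That adjusting for concomitant treatment would bias the estimate.** This would follow only if treatment started or changed after randomisation were used. The rule speaks of baseline indicators, and Table 2 places concomitant treatment among pre-treatment characteristics. One clarifying phrase is enough.
- **That site is left out of the model.** The article says a site-by-group interaction will be tested; it does not say that a site main effect is excluded.
- **That the rule inflates false positives.** In the simulation the triggered rule's type I error was at or below the nominal 5%.

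It is also fair to say that the article does not establish age, sex or HbA1c as predictors of 24-h UP change once baseline 24-h UP is in the model; being named for imputation does not prove it. If the correlations are near 0.1, the power at stake is negligible (80.7% against 80.3%).

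What remains is a stated rule, not a detail left to another document: adjustment is required when imbalance is observed, and the list of candidates is open.

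**Conclusion.** The point holds in this form: apart from baseline 24-h UP, the adjustment set depends on an undefined observed imbalance and an open list. That is at odds with the plan's stated purpose and worth correcting, but it does not undermine the primary ANCOVA.

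On size, with an assumed p < 0.05 trigger, chance alone would fire the rule in about 14% of correctly randomised trials for three covariates. It would do so in up to about 49% if all 13 named Table 2 rows could trigger it and were independent, or 34% to 40% if they amount to 8 to 10 independent tests. A reader might infer that about half of such trials would switch model, but that treats the upper bound as the expected value.

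The precision forgone depends on prognostic strength that the article does not report. Under the assumed 0.45 SD effect, triggered adjustment gives 80% to 83% power across correlations of 0.1 to 0.4, while always including the same three covariates gives 81% to 99.6%. The top of that range assumes very strong predictors.

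**What to change.** Before unblinding for the final analysis:

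1. Delete the imbalance trigger from Overall principles and the p-value column from Table 2; keep the descriptive baseline summaries.
2. Name one fixed primary model: ANCOVA with baseline 24-h UP plus a short prespecified set, used whatever the baseline table shows. Age, sex and baseline HbA1c are an obvious example, since all three are already named for the imputation model.
3. If concomitant treatment is to be a covariate, restrict it to values recorded before randomisation.
4. Label any adjustment prompted by an observed imbalance as a sensitivity analysis, and state that the fixed model gives the primary result.

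The cost is wording and a few degrees of freedom. With 120 patients analysed, a model with intercept, group and baseline 24-h UP leaves 120 − 3 = 117 residual degrees of freedom; adding age, sex and HbA1c leaves 120 − 6 = 114. No new data are needed.

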### Definition of analysis sets

#### Full analysis set

Patients who have received treatment at least once and meet the primary objective after treatment will be included in the fully analysis set (FAS).

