#### Per protocol set

The subjects who were selected in the FAS and received at least 50% of scheduled treatment with no major protocol violations will be included in the per protocol set (PPS). The PPS will be determined prior to the unblinding of the data for the final analysis and will include the following:

All visits planned and the main data completed.

The inclusion satisfied and the exclusion inapplicable.

No significant violations of the trial protocol occurred (described in adherence and protocol deviations).

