#### Safety set

The safety analysis will analyze all the patients who used the intervention drug at least once and underwent one safety assessment.

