### Imputation of missing data

Multiple imputations will be used for subjects with missing primary outcome data. Variables will be included in the multiple imputations, including the baseline 24-h UP, 24-h UP every 4 weeks, HbA1c, age, sex, and the characteristics and possible influencing factors of 24-h UP change. The missing data will be imputed five times. For missing secondary and safety outcomes, the results will be analyzed according to the actual data; the missing data will not be imputed nor will the model be adjusted. Furthermore, we will conduct a per-protocol analysis that excluded those with missing outcome data.

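### As worded, the full analysis set is defined by a post-treatment result on the primary outcome; it should be redefined without reference to the outcome before unblinding

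*Protocol article*

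**What the plan says.** Under Full analysis set the article states: "Patients who have received treatment at least once and meet the primary objective after treatment will be included in the fully analysis set (FAS"). No section says what meeting the primary objective means for an individual patient, and none corrects the phrase.

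The other efficacy analyses depend on this set:

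- Primary outcome analyses: "The primary analysis will be conducted in the FAS and PPS". The outcome is defined there as well: "The change in 24-h UP (mg/24 h) is the primary outcome", measured at weeks 0, 4, 8, 12, 16, 20 and 24.
- Per protocol set: it is drawn from "The subjects who were selected in the FAS and received at least 50% of scheduled treatment with no major protocol violations", so it lies inside the FAS.
- Secondary outcome analyses use the FAS and PPS, and Baseline characteristics describes the sample on the FAS.

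Under Imputation of missing data: "Multiple imputations will be used for subjects with missing primary outcome data". The same section adds: "we will conduct a per-protocol analysis that excluded those with missing outcome data".

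**The concern.** A full analysis set is meant to stay close to the randomised population. This sentence makes entry depend on something observed after randomisation and, as written, on the outcome being analysed. Three consequences follow if it is applied as printed.

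- Patients who did not do well leave both arms, and more leave the arm that does worse. The between-group comparison is distorted and the planned within-group comparisons overstate improvement.
- The per-protocol set gives no protection, because it inherits the same condition.
- The imputation rule loses its purpose, because patients with a missing outcome are not in the set.

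Even if the sentence is a slip of language, the primary population is left open to more than one reading. The article says in its Background that the plan exists to prevent data-driven interpretation, so the choice should not still be open when the data are seen.

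**Working it through.** The article gives no effect size, standard deviation, power or dropout rate and refers to the earlier protocol for the sample size. There is therefore no stated figure to reproduce. The main check sets the sections side by side.

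**Literal reading**

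1. FAS entry needs one treatment plus a met objective after treatment.
2. The primary analysis runs in the FAS and in the PPS, and the PPS is a subset of the FAS. Both carry the condition.
3. The per-protocol analysis drops patients with missing outcomes, so imputation can operate only in the FAS.
4. A patient with no week-24 value cannot be shown to have met a week-24 objective. That patient is outside the FAS, and the imputation has almost no one to act on.
5. Table 3 has a failure category (Invalid). Assume the objective is Table 3's lowest success level, "24-h UP reduction ≥ 20" per cent. Then that category is empty at the deciding time point and the efficiency rate is 100% in both arms.

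**Likely intended reading (at least one post-treatment 24-h UP value)**

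1. Selection on response disappears.
2. A patient with, say, a week-8 value but no week-24 value is in the FAS and can be imputed from the 4-weekly values.
3. A treated patient who leaves before the week-4 collection has no post-treatment value and is excluded by a post-randomisation event. The imputation rule has no such limit.
4. Size: the rate of such losses is not given. At assumed rates of 2%, 5% and 10% of 120, the numbers are 120 × 0.02 = 2.4, 120 × 0.05 = 6 and 120 × 0.10 = 12 patients.

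**Illustration of the literal reading only**

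Assumed, not from the documents: the log of the week-24/baseline ratio is normal with SD s = 0.6; geometric mean ratios r are 0.60 (SZF) and 0.80 (irbesartan); only patients with a fall of at least 20% are kept. From the documents: 60 per arm and two-sided alpha 0.05.

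Formulas: a = (log 0.8 − log r)/s; share kept = Φ(a); λ = φ(a)/Φ(a); mean log ratio among those kept = log r − sλ; their variance = s²(1 − aλ − λ²).

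| | SZF | Irbesartan |
|---|---|---|
| a | 0.288/0.6 = 0.479 | 0 |
| Share kept | 0.684 | 0.500 |
| λ | 0.520 | 0.798 |
| Mean log ratio, kept | −0.511 − 0.312 = −0.823 | −0.223 − 0.479 = −0.702 |
| Geometric mean ratio, kept | 0.439 | 0.496 |
| Variance, kept | 0.173 | 0.131 |

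- True log difference: log(0.60/0.80) = −0.288, a ratio of 0.75.
- Log difference among those kept: −0.823 + 0.702 = −0.121, a ratio of 0.886, or 42% of the true log difference.
- The irbesartan arm's true 20% fall appears as about 50% (1 − 0.496).
- Power with everyone: SE = 0.6 × √(2/60) = 0.110; Φ(0.288/0.110 − 1.96) ≈ 0.75.
- Power among those kept: n = 60 × 0.684 = 41 and 60 × 0.5 = 30; SE = √(0.173/41 + 0.131/30) = 0.093; Φ(0.121/0.093 − 1.96) ≈ 0.26.

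The range was checked by simulation over SD 0.4, 0.6 and 0.8 and ratio pairs 0.5 vs 0.7, 0.6 vs 0.8 and 0.7 vs 1.0. The better arm keeps 57–88% and the worse arm 29–63%. The difference among those kept is 34–56% of the true log difference. Power goes from 0.51–1.00 down to 0.16–0.85.

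**The case against.** The strongest reply is that nobody intends a responder-only analysis. Table 3 keeps a failure category and an efficiency rate is to be calculated, which makes sense only if failures are in the set. The imputation uses 4-weekly urinary protein values, which presupposes patients with partial follow-up. The sentence itself contains another slip (fully for full). One dose plus one post-baseline measurement is a familiar FAS definition, and under it most of the conflict with imputation goes away. The article also condenses a plan that is not shown.

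Much of this stands. A reader might infer that the trial will in fact analyse only responders, or that the rule is tilted towards SZF. The documents support neither. Their other sections point to a measurement requirement, and in the illustration the between-group difference moves towards the null.

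A reader might also infer that the safety set shares the flaw, because laboratory panels fall at baseline, week 12 and week 24. The text does not bear that out. It reads: "The safety analysis will analyze all the patients who used the intervention drug at least once and underwent one safety assessment". It does not say that the assessment must be post-baseline or a laboratory panel, a baseline panel is scheduled, and the Safety analyses section tabulates all adverse events during treatment.

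The reply does not make the printed rule sound. The article presents itself as the pre-determined analysis plan, the measurement wording appears nowhere in it, and the likely reading still removes treated patients without a post-baseline value.

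**Conclusion.** The point holds in two steps. As printed, the FAS rule selects the primary analysis population on its own outcome and contradicts the imputation rule; no other section repairs it. On the likely intended meaning, what remains is narrower: treated patients who leave before week 4 are excluded by a post-randomisation event, while the imputation section sets no such limit.

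The size cannot be established from the documents. The fall from a ratio of 0.75 to 0.89, and from power of 0.75 to about 0.26, illustrates the literal wording under an assumed threshold, effects and SD. It is not a forecast for this trial. On the likely reading the loss is 6 of 120 patients per 5% early loss, with the rate assumed and no bias estimated. The correction is still needed, because the sentence decides who enters every efficacy analysis.

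**What to change.** Before unblinding, replace the FAS sentence with wording that does not refer to the outcome, for example: all randomised patients who took at least one dose, analysed as randomised; missing week-24 24-h UP is multiply imputed as described in the missing-data section. This also settles how patients with no post-baseline value are handled. The PPS can stay as a subset of the corrected FAS, and the safety set needs no change on this account.

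The cost is a wording amendment and a few more patients passing through an imputation already planned. The drawback is that patients with no post-baseline value would be imputed from baseline data alone (the listed variables include baseline 24-h UP, HbA1c, age and sex), so their number should be reported by arm.

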#### Per protocol set

The subjects who were selected in the FAS and received at least 50% of scheduled treatment with no major protocol violations will be included in the per protocol set (PPS). The PPS will be determined prior to the unblinding of the data for the final analysis and will include the following:

All visits planned and the main data completed.

The inclusion satisfied and the exclusion inapplicable.

No significant violations of the trial protocol occurred (described in adherence and protocol deviations).

